#### Assignment of interventions: allocation

### Sequence generation {16a}

We will use simple randomization at the kindergarten level. A random list of 66 elements will be created externally via Efron’s biased coin [40] implemented in PASS, where half of the numbers will be Nor-SSEL and the other half will have additional play time.

### Concealment mechanism {16b}

Our team of recruiters will lead the workshops and will be blinded to a random list of 66 elements created by someone external to the Norwegian team before the workshops. This list will be kept in a sealed envelope stored in a safe in the USA at Yale University. After the workshop with the kindergarten leader, the kindergarten names will be organized into a list. Kindergarten leaders will return to their kindergartens to discuss the project with parents. After parents’ approval and the baseline assessment, with a minimum of 15 children, is completed by the parents and teachers, the kindergarten and research team will receive a notification about the assignment status based on the previously randomized sequence order and the completion of the baseline assessment via our online system. The system is automated to identify when the information of the 15 children is available, and only after that will the system assign the arm status based on a randomly generated list. Recruiters, hence, cannot predict the next allocation. Simple randomization and blinding of the recruiters are intended to eliminate selection bias [41].

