### Eligibility criteria {10}

To be eligible for this study, kindergartens cannot have implemented an active Nor-SSEL intervention in their kindergarten for at least the past 4 years from the start of this study and are currently “naïve” to Nor-SSEL implementation. The minimum number of 4- to 5-year-old participants we seek per kindergarten is 15. Children will participate in either the intervention or control condition as part of the pedagogical setting in the kindergarten, regardless of their involvement in the research study (i.e., data collection).

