#### Sample size {14}

Our sample will consist of 990 children aged 4 to 5 years old, distributed in groups of > 15 per kindergarten. Our sample size calculation considered the following input parameters: (1) two groups in a cluster design with an allocation ratio of 1:1; (2) a minimal detectable effect size difference of *d* = 0.27, which is the upper limit confidence interval for the effect size reported on SEL skills derived from 114 studies [1], with a mean of 0.219 (95% CI = 0.171–0.267). In this meta-analysis, the most common measure used to track SEL was the *Strength and Difficulties Questionnaire* [27], which is our primary outcome measure and rated by teachers and parents. Such a difference of 0.27 is described as a small effect size, according to the traditional benchmarks proposed by Cohen [33]. When considering only the effect sizes among the youngest (called by Cipriano et al. [1]) as elementary schools (Kindergarten [5 years old] to 5th grade [10 years old]) from exclusively randomized controlled trials and using SEL skills as outcomes, the average adjusted effect size at post-assessment was 0.241 (derived from 96 effect sizes). Therefore, our minimum expected effect size is closer to the state-of-the-art. However, the effect sizes depend on the population, outcome, and nature of the implemented intervention. Researchers have recently used data from systematic reviews and meta-analyses to recalculate the cutoffs for the difference [34–36]. (3) Intraclass coefficient correlation-derived SDQ domains ranged from 0.015 to 0.064 [37]; (4) Power was 0.8, and the adopted significance level was 0.05.

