A parallel, two-group cluster-randomized design will be used to test whether the Nor-SSEL (active intervention) mean is different from the Group “play” (active control) mean. The comparison will be made via a two-sided *t*-test with degrees of freedom based on the total number of subjects [38, 39], with a Type I error rate (*α*) of 0.05. The common subject-to-subject standard deviation for both groups is assumed to be 1, the intracluster correlation coefficient is considered to be 0.065, and the coefficient of variation of cluster sizes is assumed to be 0.65. For a power of 80%, with 30 kindergartens of 15 subjects per kindergarten in Group *Nor-SSEL* (totaling 450 children) and 30 kindergartens of 15 children per kindergarten in Group *Play* (totaling 450 subjects), the detectable mean difference (μ1 − μ2) is 0.27. Therefore, 900 children in 60 kindergartens are needed. To compensate for the potential decrease in power due to attrition, we will recruit 990 children from 66 kindergartens. The detectable difference was computed using PASS version 23.0.1.

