### Implementation {16c}

After our workshops, we will send the names of the kindergartens to the software developer, [name], and [name] to register the potential kindergartens included in the system. Then, a notification will be sent to the kindergarten leaders, notifying them that they are invited and requesting their consent from parents. As soon as parents’ consent to their children’s participation, the baseline assessment of outcomes is implemented in the system, among parents and teachers. These steps and procedures ensure that the baseline assessment is fully completed before randomization, thereby avoiding the implementation in the kindergarten with incomplete baseline data. Once the data from the 15 children per kindergarten is completed, the system will allocate the random sequence previously generated by CC. Recruiters, hence, cannot predict the next allocation. The system will display, in real time, the project team and other kindergartens participating, the number of kindergartens that have already received an assignment (without disclosing the Nor-SSEL or additional playtime status) and the number of available spots for participation in the study. This measure aims to demonstrate the transparency of the study recruitment process, given that we have limited spots available. Additionally, this procedure will prevent delays in recruitment, motivate the kindergartens to submit their data as soon as possible, and allow them to be included promptly.

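### The arm is released once 15 children have complete baselines, but 15 is a minimum and nothing closes the list first, so further children can be rated at baseline by informants who know the arm

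*Protocol article*

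**What the plan says.** All references are to the protocol article.

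- **Trigger.** Concealment mechanism {16b}: "The system is automated to identify when the information of the 15 children is available"; only then is the arm assigned. Implementation {16c} repeats it: "Once the data from the 15 children per kindergarten is completed, the system will allocate the random sequence".
- **Who learns the arm.** Concealment mechanism {16b}: "the kindergarten and research team will receive a notification about the assignment status".
- **Fifteen is a floor.** Eligibility criteria {10}: "The minimum number of 4- to 5-year-old participants we seek per kindergarten is 15". Concealment mechanism {16b} also calls 15 a minimum.
- **Planned size.** Sample size {14} describes the children as "distributed in groups of > 15 per kindergarten". It calculates with 15 per kindergarten, and "the coefficient of variation of cluster sizes is assumed to be 0.65". The recruitment target is 990 children in 66 kindergartens.
- **Assurance on timing.** Implementation {16c} says that its steps guarantee a complete baseline before randomization. Who will be blinded {17a} says that researchers stay blind until baseline has been assessed.
- **Informants.** The same blinding section says that parents and teachers, who supply the outcomes, are not masked.

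**The concern.** The release rule counts to a fixed number; it does not wait for a closed list. Where a kindergarten has more than 15 participating children, the rule is met while some baselines may still be open. The kindergarten is then told its arm, and the remaining ratings are made by people who know it.

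Two kinds of bias are possible, and they act differently. Arm-aware baseline ratings distort the starting value; under Statistical methods {20a} baseline is the first of three repeated scores in the primary model, so the estimated change is affected directly. Consent given after release would instead let the arm influence which families join. No masked informant offsets either one, and neither can be repaired once the data are collected.

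Two features of the plan make the situation plausible. Implementation {16c} shows kindergartens how many places remain and intends this to speed up submission, which rewards reaching 15 quickly. Under Eligibility criteria {10} every child joins the activities whether or not the family is in the research, so a late joiner is practically possible.

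**Working it through.** **1. The timing statements side by side.** The trigger is complete data on 15 children. The assurance is that baseline as a whole is finished first. The two agree only if no kindergarten has a 16th participant, or if a further rule makes the system wait for everyone who has consented. The document states neither: it sets no maximum, no closing date for consent, no lock on baseline and no rule for a child added later.

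Implementation {16c} puts consent before baseline, child by child. Late rating therefore follows wherever a 16th child's baseline is still open when the 15th is completed. Late consent is not excluded, but it does not follow from the trigger, because that child's parents may already have agreed.

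Participant timeline {13} lists the first SDQ under a post-allocation heading. That may be only a column label, and the point does not rest on it.

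**2. How many children could be affected.** From the target, 990/66 = 15.0 per kindergarten. With a floor of 15 everywhere, meeting the target exactly leaves no child beyond the 15th. If the average is m > 15, the share not covered by the trigger is at most (m − 15)/m. The values of m are assumptions:

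| m | (m − 15)/m |
|---|---|
| 15 | 0% |
| 16 | 1/16 = 6% |
| 18 | 3/18 = 17% |
| 20 | 5/20 = 25% |
| 25 | 10/25 = 40% |

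**3. The plan's own detectable difference.** Inputs from Sample size {14}: m = 15, 30 kindergartens per arm (450 children), ICC 0.065, CV 0.65, SD 1, two-sided α 0.05, power 80%.

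- Design effect for equal sizes: 1 + 14 × 0.065 = 1.91.
- L = m·ICC/(m·ICC + 1 − ICC) = 0.975/1.91 = 0.510.
- Relative efficiency for unequal sizes: 1 − CV²·L·(1 − L) = 1 − 0.4225 × 0.510 × 0.490 = 0.894.
- Design effect: 1.91/0.894 = 2.136.
- Detectable difference: (1.960 + 0.842) × √(2 × 2.136/450) = 2.802 × 0.0974 = 0.273.

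The stated 0.27 reproduces. With a fixed 15 (CV 0), the result is 2.802 × √(2 × 1.91/450) = 2.802 × 0.0921 = 0.258, with 83% power at 0.27.

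**4. Consistency of the size assumptions.** If no kindergarten is below 15 and the mean is 15, every kindergarten has exactly 15 and the CV is 0. A mean of 15, a minimum of 15 and a CV of 0.65 therefore cannot all hold.

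**The case against.** The strongest reply is that Concealment mechanism {16b} can be read as two conditions, baseline complete and at least 15 children, with 15 necessary but not sufficient. The assurance in Implementation {16c} and the blinding statement both support that intention. This stands as a reading of intent. It does not settle the matter, because Implementation {16c} also describes allocation as following once the 15 are complete, and an automated system will do what its rule says.

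A second reply is that the affected group may be empty, since 990/66 is exactly 15. This also stands as a limit on size. Against it, Sample size {14} plans for more than 15 per kindergarten and for varying sizes, and no stopping rule at 15 is given.

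A reader might infer more than the document supports:

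- **That children beyond the 15th will be consented and rated after allocation.** The document sets no timing for them. Late rating is possible; late consent is less certain still.
- **That a definite bias can be quoted.** Any figure needs an assumed difference between arms among late-rated children, and the document gives no basis for one.
- **That a minimum of 15 with CV 0.65 requires very large kindergartens, with a mean of about 43.** That holds for a shifted exponential only. If 10% of kindergartens have 56.5 children and 90% have 15, the mean is 0.1 × 56.5 + 0.9 × 15 = 19.15, the SD is √(0.1 × 0.9) × 41.5 = 12.45, and the CV is 0.65.
- **That the trial is underpowered for this reason.** The stated figure reproduces, and it is conservative if size is fixed at 15.

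**Conclusion.** The concern holds as an open gap in the concealment procedure and an internal conflict on timing. The stated trigger protects the first 15 children in each kindergarten and says nothing about the rest, so it does not deliver the assurance given for baseline as a whole. It does not establish that post-allocation enrolment will occur.

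The size runs from no children, if every kindergarten stops at 15, up to (m − 15)/m for an average size m that would have to be assumed. The direction and amount of any resulting bias cannot be derived from the document.

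The inconsistency in cluster sizes is secondary. It calls for a corrected description; the target of 990 children need not change.

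**What to change.** Change the trigger in Concealment mechanism {16b} and Implementation {16c}. The arm is released only when the kindergarten's consent list is closed and the parent and teacher baselines of every consented child are locked, with at least 15 children. State that children consented after release are not in the primary analysis set; they can still join the activities, as Eligibility criteria {10} already allows.

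In Sample size {14}, state a size assumption that agrees with the entry rule: either a fixed 15 with CV 0, or an expected mean above 15 with a CV that matches it.

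The cost is one change to the system's rule and a few sentences. Allocation will come somewhat later in larger kindergartens; the document gives no consent timetable from which to say by how much. The Trial status section gives protocol version 1, not yet recruiting, so on that status the change can be made before any arm is released.

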### Implementation {16c}

After our workshops, we will send the names of the kindergartens to the software developer, [name], and [name] to register the potential kindergartens included in the system. Then, a notification will be sent to the kindergarten leaders, notifying them that they are invited and requesting their consent from parents. As soon as parents’ consent to their children’s participation, the baseline assessment of outcomes is implemented in the system, among parents and teachers. These steps and procedures ensure that the baseline assessment is fully completed before randomization, thereby avoiding the implementation in the kindergarten with incomplete baseline data. Once the data from the 15 children per kindergarten is completed, the system will allocate the random sequence previously generated by CC. Recruiters, hence, cannot predict the next allocation. The system will display, in real time, the project team and other kindergartens participating, the number of kindergartens that have already received an assignment (without disclosing the Nor-SSEL or additional playtime status) and the number of available spots for participation in the study. This measure aims to demonstrate the transparency of the study recruitment process, given that we have limited spots available. Additionally, this procedure will prevent delays in recruitment, motivate the kindergartens to submit their data as soon as possible, and allow them to be included promptly.

## Assignment of interventions: blinding

### Who will be blinded {17a}

Researchers will be blinded to the link between kindergarten and the assigned randomization until the baseline is assessed. After that, the research team will know the kindergarten’s random status and allocate them to receive the training in the Second Step. Blinding informants in this context is not possible. Participants are not masked to the intervention status; teachers and parents are the primary informants of the outcomes.

### Procedure for unblinding if needed {17b}

N/A: Since blinding only occurs at the point of data analysis, there is no need for unblinding.

#### Data collection and management

### Plans for assessment and collection of outcomes {18a}

Only quantitative data, based on scales and questionnaires, will be collected throughout the one-and-a-half-year follow-up period. All outcomes of intervention effectiveness will be measured at baseline, immediately after the 28 weeks of the intervention, and 7 months after transitioning to the first grade (approximately 1 year after the intervention’s completion). Math and reading grades will be collected at the end of the first grade.

### Plans to promote participant retention and complete follow-up {18b}

Parents and teachers will receive notifications about the pending information throughout the evaluation period, which will last for one and a half years. The research group will maintain direct contact with the kindergartens, discuss our progress in organizing online workshops and in-person seminars, and report on our progress between assessment waves to engage parents.

### Data management {19}

The study activities ensure that research data are stored, backed up, managed, and curated securely, in line with the GDPR, national data protection legislation, and local institution data protection policies. All the data will be collected through the web application. Therefore, there is no transportation of paper data in sealed envelopes, locked boxes, or in locked cabinets. Questionnaires and consent will be administered via password-protected devices by teachers and parents at the field site (kindergarten and at home), and data will be automatically uploaded into a secure server through the officially approved web-based survey tool *Nettskjema*, which ensures proper data protection services [42]. The data will be deidentified before analysis to ensure the confidentiality of the participants, with identifiers kept separate from the research data and linked through unique codes.

Personal information—such as name, email address, and role in the project (e.g., parent, teacher, or kindergarten student)—will be stored separately (in Nettskjema) from the questionnaire data. Children’s and parents’ full names will be used as the basis for generating a unique identifier for each child, which consists of eight characters. This code will be integrated by matching using the Levenshtein algorithm, which can identify similarities between a set of characteristics to match children’s assessments over time without disclosing sensitive information [43]. This code enabled the researchers to match individual questionnaires from different evaluation time points and raters (parents and teachers’ assessment) while maintaining the anonymity and confidentiality of the participants, which is essential for a study involving such sensitive data on children’s behavior [44]. Once the data collection phase of the study is complete, the form containing personal information will be deleted to ensure that questionnaire responses cannot be traced back to individual participants.

Nettskjema is the primary data storage platform and will be integrated into the web application via the Nettskjema API. All data collected through the web application will be submitted directly to Nettskjema as form entries and stored accordingly. Electronic records from data collection will be exported from the respective platforms to secure servers at Nettskjema. Non-electronic data, such as letters of intention to participate from the kindergartens, will be stored in locked fire-safe 6-digit filing cabinets at Østfold University College.

### Confidentiality {27}

We will use a unique participant number for the research data instead of the names of the children, parents, and teachers. Personal identifiers will be collected only for informed consent, operational needs, and logistics (e.g., participant tracing by intervention staff or during follow-up visits). Personally identifiable information (e.g., names and phone numbers) will not be shared with other organizations outside of the research team. It will be destroyed after the study unless it is required for follow-up and/or future studies, and parents have consented to this. Confidentiality will be maintained by delinking all personal identification from the final datasets used for analysis. All anonymized data will be retained for 5 years, per the following ethical standards, and all non-anonymized data will be disposed of upon completion of the study. Since only de-identified quantitative web application engagement data are provided to the research team, we foresee minimal risks to participants.

### Plans for collection, laboratory evaluation, and storage of biological specimens for genetic or molecular analysis in this trial/future use {33}

N/A: No biological specimens will be collected in this study.

#### Statistical methods

### Statistical methods for primary and secondary outcomes {20a}

Due to the longitudinal (measured by three repeated raw continuous scores) and multilevel design (children nested in schools), two multilevel mixed-effects models will assess the intervention’s effectiveness on primary and secondary outcomes. We will use the maximum-likelihood estimator and, therefore, invoke the full-information maximum likelihood method to address missing data, assuming a missing mechanism of missing at random. The residuals will be a priori specified with a first-order autoregressive structure to account for within-subject correlation across time points (three repeated time points).

For all outcomes, an unstructured covariance matrix will be used to estimate the covariance between the random intercept (baseline assessment of the outcome) and random slope for time (i.e., potential speed of the improvement on the outcomes) at the children-level, allowing for maximal flexibility in modeling their relationship without imposing symmetry or independence.

Depending on the distribution of the outcomes, non-linear models can be implemented; however, we do not have a specific a priori model for this approach, as it is necessary to evaluate the distributional features of the observed data.

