## Methods: participants, interventions and outcomes

### Study setting {9}

The trial will be conducted in Norway, with kindergartens across the southeastern region prioritized in the cluster selection. The clusters represent each kindergarten in the two conditions. The intervention and control conditions will be implemented, and data will be collected from 66 kindergartens in Norway.

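### The primary model names schools rather than the randomized kindergartens as the cluster and specifies random effects at child level only, so the kindergarten term is misnamed and left unspecified

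*Protocol article*

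**What the plan says.** Protocol article, Study setting {9}: "The clusters represent each kindergarten in the two conditions". Sequence generation {16a}: "We will use simple randomization at the kindergarten level". Sample size {14} allows for clustering by kindergarten, with an ICC of 0.065, 15 children per kindergarten and a coefficient of variation (CV) of cluster size of 0.65.

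The primary model is defined only in Statistical methods for primary and secondary outcomes {20a}. That section justifies the model by the longitudinal data and by a "multilevel design (children nested in schools), two multilevel mixed-effects models will assess" effectiveness. It then fixes two pieces of covariance structure: first-order autoregressive residuals within the child, and an unstructured covariance between a random intercept and a "random slope for time (i.e., potential speed of the improvement on the outcomes) at the children-level". It states no kindergarten-level variance term.

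Trial design {8} and Outcomes {12} use school for the place children move to before the third assessment (T3).

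**The concern.** The unit named in the model is not the unit randomized. Read literally, children are nested in a unit that they enter after randomization and that does not exist at the first two assessments (T1, T2). The structure that is spelled out contains nothing for the kindergarten.

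Reading schools as kindergartens with a random intercept still leaves a gap. An intercept that is constant over time cancels out of a change from baseline. The arm-by-time contrast would then treat the changes of children in one kindergarten as independent. The protocol gives reasons to expect kindergartens to differ in change: staff deliver the condition to their own group (sections {6b} and {11a}), incomplete implementation is foreseen at kindergarten level ({20c}), and unblinded teachers rate the children ({17a}).

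At stake is the main superiority test. If kindergarten variance is missing where it exists, standard errors are too small, confidence intervals under-cover, and false claims of superiority exceed 5%.

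**Working it through.** **Inputs from Sample size {14}.** Two-sided α = 0.05; "Power was 0.8, and the adopted significance level was 0.05"; "a minimal detectable effect size difference of *d* = 0.27"; SD 1; ICC 0.065 for planning, with a cited range of 0.015 to 0.064; m = 15; CV = 0.65; 30 kindergartens (450 children) per arm.

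**Step 1: the plan's own figure.** With L = m·ICC/(m·ICC + 1 − ICC) = 0.975/1.91 = 0.5105, the design effect is

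DE = [1 + (m − 1)ICC] / [1 − CV²·L(1 − L)] = 1.91 / [1 − 0.4225 × 0.2499] = 2.135.

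SE = √(2 × 2.135/450) = 0.0974. With 898 degrees of freedom the detectable difference at 80% power is 0.273, and power at 0.27 is 79.1%. The stated 0.27 is reproduced. The sample size therefore already allows for kindergarten clustering.

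**Step 2: kindergarten left out, one time point.** Actual α = 2[1 − Φ(1.96/√DE)], m = 15. The simple CV formula is DE = 1 + [(1 + CV²)m − 1]ICC.

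| ICC | Cluster sizes | DE | Actual α |
|---|---|---|---|
| 0.015 | equal: 1 + 14 × 0.015 | 1.210 | 7.5% |
| 0.015 | CV 0.65, formula of step 1 | 1.293 | 8.5% |
| 0.015 | CV 0.65, simple formula | 1.305 | 8.6% |
| 0.065 | equal: 1 + 14 × 0.065 | 1.910 | 15.6% |
| 0.065 | CV 0.65, formula of step 1 | 2.135 | 18.0% |
| 0.065 | CV 0.65, simple formula | 2.322 | 19.8% |

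A simulation with 60 clusters gave 7.2-7.9% at ICC 0.015 and 16.2-19.0% at ICC 0.065.

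**Step 3: kindergarten intercept only, arm-by-time contrast.** Let rc be the correlation over time of the kindergarten effect and r the within-child correlation inside a kindergarten. The protocol gives neither; r = 0.5 and 0.7 and the rc values below are assumptions. The ICC of the change is

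ICC_change = ICC(1 − rc) / [ICC(1 − rc) + (1 − ICC)(1 − r)],

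and DE = 1 + (m* − 1)·ICC_change, with m* = 15 for equal clusters or 15 × (1 + 0.65²) = 21.3 for CV 0.65. At ICC 0.065:

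| rc | r | ICC_change | DE (m* = 15; 21.3) | Actual α |
|---|---|---|---|---|
| 1 | either | 0 | 1; 1 | 5% |
| 0.8 | 0.5 | 0.0271 | 1.38; 1.55 | 9.5%; 11.5% |
| 0.8 | 0.7 | 0.0443 | 1.62; 1.90 | 12.4%; 15.5% |
| 0.5 | 0.5 | 0.0650 | 1.91; 2.32 | 15.6%; 19.8% |
| 0.5 | 0.7 | 0.1038 | 2.45; 3.11 | 21.1%; 26.7% |

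At ICC 0.015 the same calculation gives about 6-7% for rc = 0.8 and 7-11% for rc = 0.5.

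**Step 4: degrees of freedom.** The sample-size section plans a "two-sided *t*-test with degrees of freedom based on the total number of subjects [38, 39], with a Type I error rate (*α*) of 0.05". With 66 kindergartens, referring a cluster-level statistic to 1.96 instead of t on 64 degrees of freedom gives an actual α of about 5.4%, so this matters little.

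**The case against.** The strongest reply is that the text does not exclude the kindergarten. It calls the model multilevel because children sit inside a higher unit, and such a model would ordinarily carry that unit. The child-level phrase qualifies the intercept-slope covariance and does not say that no other random effect is fitted. Schools is probably loose wording: the dissemination section also speaks of participating schools, although only kindergartens are recruited, and two of the three assessments precede school entry. A condensed article may also leave the full list of random effects to an analysis plan.

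Much of this stands. A reader might infer that the kindergarten is absent from the error term and that the primary test therefore runs at some fixed inflated level. The documents support neither inference. The term is unspecified, not excluded, and the size depends on which model is fitted, on the ICC, and on correlations over time that the protocol does not give. With a kindergarten intercept and constant kindergarten effects there is no inflation.

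It does not remove the point. The section does not defer the covariance structure. It fixes part of it in advance, names a unit other than the randomized one, and leaves T3 membership open once children have moved. Two analysts could fit different models from the same text, and the loose-wording reading still leaves kindergarten variance in change unaddressed.

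**Conclusion.** The concern holds as a defect of specification in the primary model. The cluster is misnamed, and no kindergarten-level random effect is stated, although randomization and sample size both rest on the kindergarten.

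The consequences are conditional. Complete omission would take a single-wave 5% test to about 7-9% at the lowest cited ICC (0.015) and to about 16-20% at the planning ICC (0.065), which lies just above the cited range. With a kindergarten intercept only, the arm-by-time test ranges from 5% (constant kindergarten effects) to about 10-16% (autocorrelation 0.8) or 16-27% (autocorrelation 0.5) at ICC 0.065. The intercept-only figures rest on assumed correlations. They show how sensitive the test is and are not estimates for this trial.

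**What to change.** In Statistical methods {20a}, replace the reference to schools with children nested in the kindergarten of randomization, keeping that membership at all waves including T3. Specify a kindergarten random intercept and a kindergarten-by-time random effect, in addition to the child-level covariance already planned. Cluster-based degrees of freedom can be stated in the same sentence; with 66 clusters this is a minor addition.

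The cost is a few words, in a protocol whose status is not yet recruiting, and slightly wider confidence intervals than a model without these terms would give. The sample size already allows for kindergarten clustering at a single time point.
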